### Participant Recruitment

Recruitment through AEIOU: We will first submit for ethical approval of the research project through AEIOU. Once approved, the AEIOU Research Manager ([name]) will identify parents of children attending AEIOU centres who meet the criteria outlined above (i.e. aged 4- to 5-years old). Parents identified as meeting these inclusion criteria will be provided with a letter of invitation, an information sheet and consent form (all attached) to inform them of the study.

Social Media: An invitation to participate in this research study will be made available on our social media page (Autism Centre of Excellence Griffith University Facebook page). The text will read as follows:

Are you a parent of a child who will be starting school in 2021 in South East Queensland? We're looking for parents to take part in a trial of a 6-session parent intervention to reduce (or prevent) anxiety in children with autism. For more information, email [[contact]](mailto:[contact]).

### Participants

64 parents of children with autism (aged 4- to 5-years). The sample size is deemed appropriate for this type of study design and is considered large enough to identify any significant differences between the two groups (intervention vs. control).

Confirmation of autism diagnosis: All children in AEIOU centres have an autism diagnostic assessment measure undertaken at intake (the ADOS; Autism Diagnostic Observation Schedule); children will only enter into this study if they meet the autism cut-off on this measure. If they are recruited through social media, we will conduct the ADOS at Stage 1 to confirm diagnosis and only offer the intervention if children meet the diagnostic cut-off on this measure.

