To determine group allocation, each participating family on the database will be allocated a random number via a random number generator. This will then be used to evenly distribute the participants across the two conditions, with those assigned an odd number placed in the intervention group ( $n = 32$ ), and even numbers placed in the control group ( $n = 32$ ).

All participants, regardless of their group allocation, will complete the measures listed in Section 3 at Stage 1 (initial assessments), Stage 3 (short-term follow-up) and Stage 4 (one-year follow-up). The longitudinal nature of this study allows for us to determine the short-term and longer-term effects of the CLK program on the anxiety levels of children with autism. We are also able to examine whether participation in this intervention had any impact on the more distal constructs of, for example, maternal stress (DASS).

Participants will be recruited and assessed in three waves:

1. Beginning January 2020: Recruitment will focus on social media
2. Beginning February 2020: Recruitment via social media and AEIOU
3. Beginning June 2020: Recruitment via social media and AEIOU

For each wave, participation will begin with the completion of the initial assessments (see Section 3), followed by the modified CLK intervention for those in the intervention group (administered as per the manual), short-term follow-up assessments (within two months of CLK program completion) and long-term follow-up assessments (one-year later). The initial three stages of the study will occur over a 5- to 6-month time frame, with the final follow-up assessments occurring one year later.

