#### Procedure after consent is given

Upon obtaining consent, the postdoctoral research fellow / project manager ([name]) will contact consenting parents and provide a link to the online questionnaires. Parents who complete the initial assessments will be advised of their randomly allocated group membership (intervention vs. control). Those in the intervention group will be asked to select a parent group at a convenient location and times for them. All parents will be reminded of the contact details for the research team.

Although parents have provided their informed consent to participate in the research, their children will be asked to provide their assent (where possible) prior to completing the direct child assessments. Given that the verbal ability of some children may be relatively low, their vocalisations and physical behaviours will be taken into consideration when determining their assent. The child's parent(s) will also be present during these assessments, so can assist in interpreting the child's behaviours. At all times, the child's verbal and non-verbal behaviours will be observed. If at any point either the researcher or child's parent feel that the child would like to stop or have a break, the researcher will respond accordingly by either discontinuing or pausing the assessment. Additionally, children with autism often communicate using picture communication symbols. Where appropriate, we will make a "break" symbol available, so the child is able to pause/stop the assessments by presenting this symbol.

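### For social-media recruits the ADOS cut-off governs the offer of the intervention, not study entry, so the protocol permits children below it to be handled differently in the two arms

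*Protocol*

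**What the plan says.** The rule is in the Protocol, section 5, Participants, under the confirmation of diagnosis. It differs by recruitment route:

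- **AEIOU centres.** The ADOS is done at centre intake, and "children will only enter into this study if they meet the autism cut-off on this measure". This is a condition of study entry, so it applies before either arm.
- **Social media.** Here "we will conduct the ADOS at Stage 1 to confirm diagnosis", and the team will "only offer the intervention if children meet the diagnostic cut-off on this measure". This is a condition of receiving treatment. Study entry is not mentioned.

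Three other statements bear on how the second rule works:

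- Methodological Approach, on allocation: "each participating family on the database will be allocated a random number via a random number generator", with odd numbers going to intervention and even numbers to control, 32 in each. No time point and no eligibility condition are given.
- Procedure after consent is given: "Parents who complete the initial assessments will be advised of their randomly allocated group membership". The trigger is completing the assessments, not meeting the cut-off.
- Methodological Approach, on follow-up: "All participants, regardless of their group allocation, will complete the measures listed in Section 3 at Stage 1", and again at Stages 3 and 4.

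The Methodological Approach also states that control families do not take part in the program. No section says what happens to a social-media child who falls below the cut-off, in either arm.

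**The concern.** A rule that restricts who is offered the intervention can act only on families who would otherwise be offered it, and those are all in the intervention arm. Read as written, the cut-off has no effect on a control family recruited through social media. Eligibility, or at least exposure to treatment, then depends on the arm.

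The Methodological Approach relies on randomisation to attribute differences after the intervention to the intervention itself. That inference needs the same children to be in scope in both arms. If children below the cut-off are dropped from one arm only, the arms differ in composition for a reason other than chance. If they are kept but not treated, the intervention arm carries built-in non-treatment and the estimated effect shrinks. In both cases control may include children outside the target population, which the protocol defines as children with autism.

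**Working it through.** **Step 1. Compare the rules.**

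| Point | AEIOU route | Social-media route |
|---|---|---|
| When the ADOS is done | Centre intake | Stage 1 |
| What the cut-off controls | Study entry | Offer of the intervention |
| Arms it acts on | Both | Intervention only, as worded |
| Condition for a random number | Being a participating family | Being a participating family |
| Condition for being told the allocation | Completing initial assessments | Completing initial assessments |

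The last two rows do not repair the third. Even if the number is drawn after Stage 1, no text makes meeting the cut-off a condition for receiving one.

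**Step 2. Follow a social-media child below the cut-off.**

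- Allocated to intervention: not offered the program. The child is then either (a) removed or (b) followed untreated. The text does not choose between these. The follow-up statement leans towards (b).
- Allocated to control: no rule applies, so the child is followed and measured.

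**Step 3. Illustrate the size.** The protocol gives no figure to reproduce here: no social-media share, fail rate, anxiety gap, or power basis for the 64. The only document input is 32 per arm. The rest are assumptions:

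- s = share of the sample from social media, 0.25 to 1
- f = proportion of those below the cut-off, 0.05 to 0.20
- g = difference in mean anxiety between children below and above the cut-off, 0.5 to 1 SD

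Expected number below the cut-off per arm = 32 × s × f.

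*Reading (a), removed from intervention only.* With no treatment effect, the control mean is shifted by s × f × g and the intervention mean is not, so the bias is s × f × g. Its sign follows the sign of the gap, which the documents do not give.

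*Reading (b), kept untreated.* Both arms keep the same mix, so there is no selection bias. A true effect d becomes d × (1 − s × f). Power below is for d = 0.5 SD, 32 per arm and an assumed two-sided alpha of 0.05. Without dilution it is 0.52.

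| s | f | Below cut-off per arm | (a) bias, g = 0.5 to 1 | (b) 0.5 SD becomes | (b) power |
|---|---|---|---|---|---|
| 0.25 | 0.05 | 0.4 | 0.006 to 0.013 SD | 0.494 | 0.51 |
| 0.5 | 0.10 | 1.6 | 0.025 to 0.05 SD | 0.475 | 0.48 |
| 0.75 | 0.20 | 4.8 | 0.075 to 0.15 SD | 0.425 | 0.40 |
| 1 | 0.20 | 6.4 | 0.10 to 0.20 SD | 0.40 | 0.36 |

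For the second row: 0.5 × 0.10 = 0.05; 32 × 0.05 = 1.6, leaving 30.4 against 32; 0.05 × 0.5 = 0.025 and 0.05 × 1 = 0.05; 0.5 × 0.95 = 0.475. The last row is a ceiling only, because AEIOU recruitment is planned for waves 2 and 3.

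**Step 4. Put it in proportion.** The standard error of a mean difference with 32 per arm is √(2/32) = 0.25 SD. The illustrative bias is 0.1 to 0.2 of one standard error. The ceiling of 0.20 SD is 0.8 of one.

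**Step 5. After the change.** If the cut-off is applied before allocation in both arms, the expected number below it is zero in each arm, and both the bias and the dilution vanish.

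**The case against.** The strongest reply is that this is loose wording. The Participants section opens by describing the sample as parents of children with autism, the Background describes two groups of children with autism, and the social-media advert is addressed to parents of such children. On that reading, offering the intervention simply means including the child. This is plausible as intent. But the sentence just before it uses entry language for the AEIOU route, and no other section extends the social-media rule to control.

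A reader might infer more than the text supports:

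- *That the cut-off is applied to families already allocated.* The protocol dates only the disclosure of the allocation. A number drawn after Stage 1 fits every section.
- *That failing children leave the intervention arm and stay in control.* The text withholds the program and says nothing about leaving. Their presence in control follows from the absence of a rule, not from a statement.
- *That those who score the ADOS know the allocation.* Research team members administer it and data files are limited to the project team, but no section says who generates or holds the allocation.

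Two further objections stand in part. The size rests wholly on assumptions and is small in the middle of the range. The damage may also be recoverable: the Stage 1 ADOS is planned for social-media recruits in both arms, so an analysis could be restricted to children meeting the cut-off in both. That would restore a fair comparison only if scoring was not influenced by knowledge of the allocation, and it would cost numbers. Analysis populations may be set in a statistical analysis plan that is not at hand. Entry criteria and their order relative to allocation, however, belong in the protocol.

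**Conclusion.** The point holds as a defect in what the protocol permits, not as a demonstration that ineligible children were or will be removed from one arm. The cut-off is an entry rule for one route and a treatment rule for the other. The treatment rule can act only in the intervention arm, and the sections on allocation and disclosure do not close the gap. Following the text gives either one-sided exclusion or one-sided non-treatment. Exclusion after allocation and scoring with knowledge of the allocation are possible but not shown.

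The size cannot be fixed from the documents. At an assumed 50% social-media share and 10% below the cut-off, it is about 0.025 to 0.05 SD of bias if those children are removed from one arm, or a true 0.5 SD effect diluted to 0.475 if they stay untreated. It grows in proportion to the share and the fail rate. The case for changing the text rests on the arm-dependent rule and the low cost of removing it, not on a large expected bias.

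**What to change.** - In Participants, make meeting the ADOS cut-off a criterion for study entry for both recruitment routes and both arms, replacing the condition on the offer of the intervention.
- In Methodological Approach and in Procedure after consent is given, state that the random number is generated only after Stage 1 is complete and ADOS eligibility has been recorded, and that only eligible families receive a number and are told their group.

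**Cost.** This changes wording and the order of steps. No assessment is added, since the Stage 1 ADOS is already planned for every social-media child. Social-media families below the cut-off would complete Stage 1 but would not be randomised or followed up. Replacements may be needed to reach 64: on the illustrative inputs, about 2 × 1.6 = 3.2 families across both arms.

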### Recruitment strategy:

AEIOU: The intervention centre will send information about the study to families who meet the eligibility criteria. This information will be sent via two means, firstly an email from the AEIOU Communications division and secondly a printed copy will be available via the child's centre. If needed, member(s) of the research team will offer drop-in sessions for the invited parents to ask any questions about the research.

Parents that wish to participate will complete the consent form, put it inside a sealed envelope provided with the consent materials, and then return it to the child's early intervention centre within 14 days of receiving the invitation. The Centre Manager will notify their research manager and/or the research team when envelopes have been received so that the contact information can be shared with the research team.

Social Media: An advert will be posted on our social media page (Autism Centre of Excellence Griffith University Facebook page) inviting parents of children with autism aged 4- to 5-years to participate. Parents will be asked to indicate their interest by sending an email to our project specific email address. We will then reply to this with the information and consent materials. If requested, we will also post a hard copy of this material. If needed, member(s) of the research team will offer drop-in sessions for the invited parents to ask any questions about the research.

Parents who wish to participate can complete an online consent form or print a PDF and email it or return the consent form via email or post within 14 days of receiving the invitation (date stamp on envelope used to indicate date of response). If parents choose to respond via the online consent form or email, they will be asked to complete a hard copy of the consent form when first meeting with a member of our research team (e.g. when attending the child-directed assessments).

Incentive: Parents will be provided with a gift card after their completion of each assessment stage. The value of the gift card will increase as they progress through the study: \$25 for completion of Stage 1, \$50 for Stage 3, and \$100 for Stage 4. This increase in value reflects their continued commitment to the project. It also acts as an incentive for parents to complete each of the assessment stages; this is vital as in order to determine the efficacy of the intervention, we need as many parents as possible to complete the project.

We will also provide parents with confidential research reports; one after Stage 1 (for those recruited through social media only) and after Stages 3 and Stage 4 for all participants). These will detail their child's level of IQ and adaptive functioning and can be shared with anyone they wish as it may assist in providing others with further information on their child's ability and skills.

Sample management: Parents who consent to participate based on the first social-media advert will be allocated to wave one (until this reaches capacity), with any additional parents allocated to wave two and three as needed. For wave two, invitations will be circulated to AEIOU parents (and social media if necessary). In the unlikely event that all invitations are accepted, these families will be divided across wave two and three. If only a subsample accepts the invitation, they will be allocated to wave two (until this reaches capacity), with any additional parents allocated to wave three. The AEIOU uptake rate observed here will give us a better idea of the number of potential families to circulate the study information to for the third wave.

Any parents who accept the invitation in the third round of recruitment will be allocated to wave three.

Given our staged recruitment strategy across multiple waves, it is unlikely that a large number of additional parents will wish to participate. The number of parents approached at each wave can be adjusted to reflect the number of parents who have already consented to the project. We anticipate that the three waves may not be equal in size and this has been factored into the study design and therapist availability to run groups.

#### Procedure after consent is given

Upon obtaining consent, the postdoctoral research fellow / project manager ([name]) will contact consenting parents and provide a link to the online questionnaires. Parents who complete the initial assessments will be advised of their randomly allocated group membership (intervention vs. control). Those in the intervention group will be asked to select a parent group at a convenient location and times for them. All parents will be reminded of the contact details for the research team.

Although parents have provided their informed consent to participate in the research, their children will be asked to provide their assent (where possible) prior to completing the direct child assessments. Given that the verbal ability of some children may be relatively low, their vocalisations and physical behaviours will be taken into consideration when determining their assent. The child's parent(s) will also be present during these assessments, so can assist in interpreting the child's behaviours. At all times, the child's verbal and non-verbal behaviours will be observed. If at any point either the researcher or child's parent feel that the child would like to stop or have a break, the researcher will respond accordingly by either discontinuing or pausing the assessment. Additionally, children with autism often communicate using picture communication symbols. Where appropriate, we will make a "break" symbol available, so the child is able to pause/stop the assessments by presenting this symbol.

#### Research Activities

Participants in the intervention group will attend a parent-mediated, group-based intervention designed to prevent/reduce anxiety in their children with autism. The intervention consists of six two-hour sessions spaced over a school term. The intervention has a clinician manual and a parent workbook and parents are asked to undertake some homework activities between sessions.

Parents and children will also participate in initial and follow-up assessments (stage 1, 3 and 4) that will take place approximately two weeks prior to the intervention, two weeks following the intervention, and one-year later. Children recruited via AEIOU will only require the follow-up assessments (stage 3 and 4) as they will have already completed the ADOS and MSEL during their AEIOU intake assessment. All stage 1, 2 and 3 activities will be completed by December 2020; the final follow-up will be conducted the following year (2021).

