### **3. Resources**

This study consists of four stages: initial assessment (stage 1), intervention (stage 2), short-term follow-up assessment (stage 3), and one-year follow-up assessment (stage 4). At Stages 1, 3, and 4, data will be captured from the participating parent(s) and their child.

Direct child assessments focus on gaining an understanding of the child's autism severity and cognitive ability. A trained member of the research team will administer these assessments within a 1:1 setting. At Stage 4, additional assessments will be included to address school-related skills.

Parent completed assessments consist of a series of standardised questionnaires made available online via REDCap Survey.

*Note.* Three of these assessments are administered by our partner organisation (AEIOU) as part of their existing intake assessments (marked with an asterisk below). As such, these will not be administered at Stage 1 for those participants recruited via AEIOU.

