#### Data Collection/Gathering

**Parents:** All parents will be asked to complete questionnaires at Stage 1, 3, and 4 (initial assessments, short-term follow-up and one-year follow-up). These questionnaires will be administered using REDCap so they can be completed online. The questionnaires ask parents to report on their child's anxiety, intolerance of uncertainty, repetitive behaviours, the impact anxiety may have on daily life, and other relevant constructs. Note that at Stage 1, parents recruited via AEIOU will not have to complete the Vineland caregiver questionnaire as this is administered as part of the AEIOU intake procedure.

At Stage 4, additional parent questionnaires will be added to assess their child's school-related skills (subject to approval of modification request; see Section 3). All parents will be invited to answer these items. We will provide parents with additional details regarding Stage 4 assessments closer to the time.

The standardised questionnaires completed by the parents are as follows:

- Preschool Anxiety Scale Revised (PAS-R)
- Anxiety Scale for Children with Autism Spectrum Disorder (ASC-ASD)
- Intolerance of Uncertainty Scale (IUS-P)
- Vineland Adaptive Behaviour Scales 3rd Edition (VABS-3)\*
- Repetitive Behaviour Scale – Early Childhood (RBS-EC)
- Depression Anxiety Stress Scales (DASS)
- Children's Anxiety Life Interference Scale (CALIS)
- Responses to Uncertainty and Low Environmental Structure questionnaire (RULES)
- Short Sensory Profile II
- Social Communication Questionnaire (SCQ; a measure of autism symptoms)

In addition, parents recruited via an early-intervention centre will be asked to consent to the sharing of assessment data already collected by their child's AEIOU Foundation centre. Sharing of these data will be beneficial in describing the participant group and will save repeating these assessments unnecessarily.

Specifically, the following assessment data will be requested:

- Autism Diagnostic Observation Scale-Second Edition
- Mullen Early Learning Scales
- Vineland Adaptive Behaviour Scale- Third Edition

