#### Data Analysis

All responses to the assessments will be scored as per the scoring guidelines allowing for quantitative analysis to be conducted. This will determine if there is any change in pre/post intervention scores on the measures used in the project, and will allow for comparisons between the participant groups (intervention vs. control).

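### AEIOU recruits have no Stage 1 VABS-3, ADOS-2 or MSEL, so pre/post change on these measures covers different intervals by recruitment source

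*Protocol*

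**What the plan says.** Section 3 (Resources) marks three instruments with an asterisk: ADOS-2, MSEL and VABS-3. Of these it says "Three of these assessments are administered by our partner organisation (AEIOU) as part of their existing intake assessments", and that "these will not be administered at Stage 1 for those participants recruited via AEIOU".

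Section 5 repeats the exception. For the child assessments, Research Activities says: "Children recruited via AEIOU will only require the follow-up assessments (stage 3 and 4) as they will have already completed the ADOS and MSEL". For the parent questionnaire, Data Collection/Gathering says that "parents recruited via AEIOU will not have to complete the Vineland caregiver questionnaire as this is administered as part of the AEIOU intake procedure", and asks AEIOU parents to consent to release of the intake results for all three instruments. It gives two reasons: to describe the sample and to avoid repeat testing.

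Research Activities times the assessments at "approximately two weeks prior to the intervention, two weeks following the intervention, and one-year later". Methodological Approach gives 5 to 6 months for the first three stages together.

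Two places describe Stage 1 as uniform. Methodological Approach states: "All participants, regardless of their group allocation, will complete the measures listed in Section 3 at Stage 1 (initial assessments". Direct Child Assessments in Section 3 has the research team administering ADOS-2 and MSEL at Stages 1, 3 and 4.

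Data Analysis sets out to determine "any change in pre/post intervention scores on the measures used in the project" and to compare the two groups. The list under Outcome measures includes VABS-3 but not ADOS-2 or MSEL.

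**The concern.** The label Stage 1 covers two different things. For a social-media family it is a measurement made for the trial shortly before the intervention. For an AEIOU family, on these three instruments, it is a score from centre intake. The protocol does not say when intake took place, sets no limit on the age of the score, and has no rule for repeating an old one.

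Pre-to-post change for an AEIOU child therefore runs from intake to follow-up. It takes in whatever happened between intake and the trial, including time at an early intervention centre. For ADOS-2 and MSEL, the assessing organisation also changes between the two measurements. A pre/post figure pooled over both sources would average changes over unlike periods, and the part belonging to the trial could not be separated out.

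This is more than detail that an analysis plan could supply later. A plan can choose a model, but it cannot recover a baseline that was never collected.

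**Working it through.** The protocol states no figure on this point, so there is none to reproduce. The check compares the interval from baseline to follow-up in the two recruitment sources.

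**Inputs**
- T, Stage 1 to Stage 3: 5 to 6 months (Methodological Approach). This is the length of all three stages, so it is an upper bound on the interval. A shorter T would raise the ratios below.
- g, AEIOU intake to Stage 1: not given. Assumed range 0 to 24 months.
- 64 families, 32 per arm, with no stratification by source mentioned (Methodological Approach).

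**Interval to Stage 3.** Social media: T. AEIOU: g + T. Ratio: (g + T)/T. Share of the AEIOU interval lying before the trial: g/(g + T).

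| g (months, assumed) | AEIOU interval (months) | Ratio | Share before trial |
|---|---|---|---|
| 0 | 5–6 | 1.0 | 0% |
| 6 | 11–12 | 2.0–2.2 | 50–55% |
| 12 | 17–18 | 3.0–3.4 | 67–71% |
| 18 | 23–24 | 4.0–4.6 | 75–78% |
| 24 | 29–30 | 5.0–5.8 | 80–83% |

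For example, with g = 24 and T = 5: (24 + 5)/5 = 5.8 and 24/29 = 83%.

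**Interval to Stage 4.** Adding 12 months gives 17 to 18 months for social-media children. With g = 6 the ratio is 24/18 = 1.3 to 23/17 = 1.4. With g = 24 it is 42/18 = 2.3 to 41/17 = 2.4. The mismatch is smaller but does not go away.

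**Extra variance in the arm comparison of change.** With equal SDs at both times, the variance of a change score is 2(1 − r) in SD² units, where r is the baseline-to-follow-up correlation. Assume r = 0.8 for a recent baseline, r = 0.6 for an intake score, and half the families from AEIOU. The average variance is then 0.5 × 0.4 + 0.5 × 0.8 = 0.6, against 0.4 if all baselines were recent, a ratio of 1.5. Over assumed AEIOU shares of 30% to 70% and intake correlations of 0.7 to 0.5, the ratio runs from 1.15 to 2.05.

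**Chance imbalance by source.** With arms fixed at 32 each and an AEIOU share of 0.5 (assumed), the SD of the between-arm difference in that share is √(0.5 × 0.5 × 2/32 × 64/63) = 0.126. If the pre-trial gap shifts mean change in AEIOU children by Δ, a one-SD imbalance moves the arm difference by about 0.13Δ. This averages to zero over randomisations.

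**The case against.** The strongest reply is that the trial's question concerns child anxiety. PAS-R and ASC-ASD carry no asterisk and are completed at Stage 1 by every parent. This stands: the anxiety outcomes are untouched.

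Second, sparing young autistic children a repeat assessment is a deliberate and openly stated choice, and the protocol says that the intake data help to describe the sample. ADOS-2 and MSEL are not in the outcome list. This also stands and narrows the point mainly to VABS-3. It does not answer it: Data Analysis exempts none of the measures, all three are repeated at Stages 3 and 4, and the intake score is the only baseline planned for AEIOU families.

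Third, the conflict with Methodological Approach is slight, because that sentence refers to Section 3 and Section 3 contains the exception. Agreed; the wording needs aligning and no more.

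Fourth, Data Analysis is a general statement. It does not commit to raw change scores, and baseline adjustment may be set out in an analysis plan. That is fair as regards the model, but no model supplies the missing Stage 1 VABS-3.

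Two stronger readings are tempting and should not be drawn:
- A reader might infer that the arm comparison is confounded by source. Families from both sources are randomised, so it is unbiased in expectation. What remains is added variance and chance imbalance.
- A reader might infer that change is overstated. The documents do not show a direction. MSEL is to yield a developmental quotient, and age-normed scores need not rise over a longer interval.

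The change of assessor should likewise not be carried over to VABS-3, which is a caregiver questionnaire. Nor does the protocol say that the intake records lack dates; it only sets no limit on their age.

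**Conclusion.** The point holds in a limited form. On VABS-3, ADOS-2 and MSEL, the interval from baseline to follow-up depends on recruitment source, and for AEIOU children part of it precedes the trial. If intake was 6 to 24 months before Stage 1, the interval to Stage 3 is about 2 to 6 times the social-media interval. That gap is an assumption. Near zero the problem vanishes, but nothing in the protocol ensures a short gap.

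Within-group pre/post change on these measures cannot be read as change during the trial, and a between-arm comparison of change loses precision. The variance figures rest on assumed correlations and AEIOU shares and are illustrative. The consequence falls mainly on VABS-3, the only one of the three that is a listed outcome. The weight is that of a cheap improvement, not a threat to the main result.

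**What to change.** 1. Have AEIOU parents complete the VABS-3 on REDCap at Stage 1 with the other questionnaires, as social-media parents already do.
2. Record the date of the AEIOU intake assessment and the child's age at that time.
3. Use intake ADOS-2 and MSEL as descriptors of the sample or as covariates, and state that they are not baseline scores for computing change.
4. Align Direct Child Assessments (Section 3) and Methodological Approach (Section 5) with the AEIOU exception for ADOS-2 and MSEL. Remove the VABS-3 exemption from Section 3 and Data Collection/Gathering.

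The cost is one more online questionnaire for AEIOU parents, a date field and some wording. No child is retested and no staff are added.
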